## Abstract

**Background:**

Hearing impairment is one of the most frequent chronic conditions. Persons with a hearing impairment (PHI) have various experiences during their ‘journey’ through hearing loss. In our previous studies we have developed a ‘patient journey’ model of PHI and their communication partners (CPs). We suggest this model could be useful in internet-based pre-fitting counseling of a person with hearing disability (PHD).

**Methods/Design:**

A randomized controlled trial (RCT) with waiting list control (WLC) design will be used in this study. One hundred and fifty eight participants with self-reported hearing disability (that is, score >20 in the Hearing Handicap Questionnaire (HHQ)) will be recruited to participate in this study. They will be assigned to one of two groups (79 participants in each group): (1) Information and counseling provision using the ‘patient journey’ model; and (2) WLC. They will participate in a 30 day (4 weeks) internet-based counseling program based on the ‘patient journey’ model. Various outcome measures which focuses on hearing disability, depression and anxiety, readiness to change and acceptance of hearing disability will be administered pre (one week before) and post (one week and six months after) intervention to evaluate the effectiveness of counseling.

**Discussion:**

Internet-based counseling is being introduced as a viable option for audiological rehabilitation. We predict that the ‘patient journey’ model will have several advantages during counseling of a PHD. Such a program, if proven effective, could yield cost and time-efficient ways of managing hearing disability.

**Trial registration:**

ClinicalTrials.gov Protocol Registration System NCT01611129.

## Background

The term ‘patient journey’ refers to the experiences patients go through during their disease and treatment. It is believed that understanding the ‘patient journey’ can help the clinician to gain an insight into the unique experiences of patients. In the last decade, with increased focus on patient-centered treatment approaches in healthcare, studies of the ‘patient journey’ have become popular. The ‘patient journey’ has been studied in various conditions including: Parkinson’s disease [1], locked-in syndrome [2], pertussis [3], gastrointestinal stromal tumors [4], and rheumatoid arthritis [5,6]. In our previous studies we developed ‘patient journey’ models for adults with gradual-onset [7,8] and sudden-onset [9] acquired hearing impairment.

Figure 1 shows the ‘patient journey’ model of adults with gradual-onset acquired hearing impairment [7]. This model shows that there are seven main phases in this process, which include: (1) pre-awareness; (2) awareness; (3) movement; (4) diagnostics; (5) rehabilitation; (6) self-evaluation; and (7) resolution. Manchaiah *et al*. argued that this model could help the clinicians during history taking to understand at what stage the patient might be and then to tailor the way they speak to them [7].

**Figure 1 F1:**

**‘Patient journey’ model of adults with gradual-onset acquired hearing impairment**[7]**.**

### Pre-fitting counseling

There is a range of interventions focusing on the psychosocial needs of people with acquired hearing loss. For example, counseling-based aural rehabilitation [10]; active communication education (ACE) [11], rehabilitative online education [12] and cognitive behavioral self-help program [13]. However, pre-fitting counseling is mainly used for assessing and modifying the patient’s belief, motivation and expectations towards communication and to provide information about hearing loss and choice of interventions. Such counseling sessions could be very important in the audiological enablement process [14]. Even though pre-fitting counseling sessions could be potentially beneficial in various domains, there appears to be very little or no benefit in terms of the outcome of hearing aid fitting [15,16]. However, the main reason for pre-fitting counseling is to support the person with hearing impairment (PHI) in terms of their emotional and social needs, to assess and modify attitudes and motivations and to provide information about the choice of interventions [17], rather than focusing on hearing aid outcomes.

PHI go through various unforeseen consequences during their ‘journey’ through hearing loss. In a recent study by Laplante-Lévesque *et al*. it was identified that PHI mainly use their life experiences to describe their hearing help-seeking and hearing rehabilitation process rather than the interactions with clinicians [18]. It is believed that patients’ knowledge of the journey (that is, phases and stages they may go through) may reduce their anxiety and fear [19]. This is because the ‘patient journey’ model may relate to their lived experiences rather than focusing on the audiogram, causes of hearing loss, and hearing aids. In addition, the ‘patient journey’ model also presents them with the stages or the experiences they may go through in the future.

The ‘patient journey’ model considered above corresponds to the stages of change in the ‘transtheoretical model of change’ [20,21]. There have been various attempts in the literature to facilitate the stages of change in various domains including cessation of smoking, injury prevention, and weight loss. Manchaiah suggested that the use of health behaviour change models could be useful in facilitating help-seeking in patients with hearing loss [22]. For example, according to the health belief model (HBM) five main factors: (1) perceived severity; (2) perceived susceptibility; (3) perceived benefits; (4) perceived barriers; and (5) health motivation, may influence an individual’s decisions in proactive health behaviour [23]. We suggest that making the PHI aware of the ‘patient journey’ and in particular which stages they are currently in and what to expect later on, would increase their acceptance of hearing loss and readiness to change, hence positively facilitating stages of change in reaction to the hearing loss.

Moreover, considering the above, it is reasonable to expect that the ‘patient journey’ model can be used as a counseling tool to create awareness and educate PHI and their CPs during initial consultations. This may result in various advantages such as decreased emotional and social problems, decreased anxiety and depression, increased acceptance of hearing disability, and may positively facilitate stages of change through hearing disability, which are important factors in determining the success of audiological enablement/rehabilitation.

### Internet-based audiological rehabilitation

In recent years there has been an increase in the use of the internet for seeking health-related information. Cummings *et al*. suggested that online support groups in the form of a subscription distribution list can help people with hearing loss [24]. Laplante-Lévesque *et al*. used daily internet-based communications (in the form of Emails) in addition to the usual audiological service provided to people with hearing loss [25]. Their study demonstrated that an internet-based counseling program for new hearing aid users could be interactive and effective. Moreover, they found that each participant exhibited different behaviors and shared different thoughts during internet-based audiological counseling. More recently, Thorén *et al*., in a randomized controlled study evaluated the use of a rehabilitative online education program with discussion groups for hearing aid users [12]. They observed significant differences between pre and post counseling sessions in both groups, and the effects were maintained at six months follow-up. Overall, these studies suggest that the internet may be effectively used in audiological rehabilitation.

Considering the increased use of the internet by the general population, which increases flexibility for patients to participate in such programs in their own time and preferred place, and in the interest of reducing clinicians’ contact time, we will employ internet-based counseling in this study.

This paper describes the design of a randomized controlled trial to evaluate the effectiveness of the ‘patient journey’ model in the internet-based pre-fitting counseling of persons with hearing disability.

### Aim

The study is aimed at testing the hypotheses that, during the initial consultation of the PHD:

(1) Use of the ‘patient journey’ model as an internet-based counseling tool will result in decreased hearing-related emotional and social problems.

(2) Use of the ‘patient journey’ model as an internet-based counseling tool will result in decreased depression and anxiety.

(3) Use of the ‘patient journey’ model as an internet-based counseling tool will result in increased readiness to change (or positively facilitate stages of change through hearing disability).

(4) Use of the ‘patient journey’ model as an internet-based counseling tool will result in increased acceptance of hearing disability.

## Method

### Participant recruitment and study design

Ethical approval has been received from the Research Ethics Committee, College of Human and Health Sciences, Swansea University. A study advertisement will be made (in the United Kingdom) through various sources including local/national newspapers, hearing loss charity websites and mailing lists, inviting those with acquired hearing disability who have not yet had their hearing aids and who have internet access, to participate in this study. They will be given an information sheet describing the study and directing them to the website. In the first stage, interested participants will complete an informed consent form and the online questionnaires and the first 158 participants showing scores of over 20 in the Hearing Handicap Questionnaire (HHQ) will be recruited to participate in the study (that is, showing at least mild hearing disability). The HHQ scores can range from 12 to 60, from no hearing disability to a severe degree of hearing disability. In this study a wide range of people with hearing disability (that is, mild to severe degree) will be selected. However, a minimum score of over 20 was deemed appropriate to avoid the floor effect. The participants recruited will be randomized (randomization will be done independently of the researcher, by another person) to one of the two groups: (1) Information and counseling provision using the ‘patient journey’ model; and (2) Waiting list control (WLC). In addition, in the beginning of the study an Email with clear information about the study will be sent to willing participants to ensure that they have the time to participate in the study. Data will be collected using the various outcome measures discussed below pre and post counseling sessions. Figure 2 outlines the study design.

Inclusion criteria:

▪ Age over 18 years

▪ Noticing symptoms of hearing disability

▪ Access to internet

Exclusion criteria:

▪ Already using hearing aids

▪ HHQ score 20 or below

▪ Those with additional disabilities (for example, visual impairment, learning disability, dementia, and so on) which may affect individuals’ ability to participate in an internet-based program

**Figure 2 F2:**
[figure not shown]
Flow chart showing the study design.

### Intervention

Group one will be given ‘patient journey’ counseling which is based on previous studies [7,8,26], through an internet-based counseling protocol system. The focus of this would be on lived experiences of PHD rather than technical information such as the audiogram and hearing aids. This would involve four stages of designated internet sessions and additional tasks which the patients can complete in their own time. This program should be completed within 30 days. These sessions include: Stage 1 - introduction to the concept of the ‘patient journey’ and presenting to the participants a series of questions which may help them to explore their ‘journey’ through hearing loss; Stage 2 - the ‘patient journey’ model of PHI and two case examples will be presented. The PHD will be advised to compare their ‘journey’ to the model presented and identify the similarities and differences; Stage 3 - the ‘communication partners’ journey’ model will be presented and the PHD will be asked to consider how interactions between him/her and the CP may affect various things in the physical, mental and social domains; and Stage 4 - participants will be encouraged to think about how the PHI and CP may influence each other during their ‘journey’ through hearing loss, how they can overcome some of the difficulties they may be experiencing and to think about the potential benefits and the challenges from the audiological management.

Each stage will contain a short video (that is, one to two minutes) which briefly explains the tasks. However, the information presented in the video is also available in text to make sure equal access is provided to those who may find it difficult to understand speech in the video. Having information in different formats (for example, text and video) would help in ensuring that the information is presented in an interactive manner and that it engages the users in the activity. Throughout this process, the participants will be advised to reflect (a simple guide for reflection will be provided) and maintain notes. This reflection exercise is to explore the activity limitations and participation restrictions they have and also to explore the ways in which they can overcome them. In addition, there will be an Email contact with the researcher (who is also a trained audiologist) with whom they can communicate, update their progress with the intervention and seek further assistance.

The second group, which serves as the WLC, will complete the questionnaire at the beginning of the study and after 30 days will be provided with the same intervention as the other group. During the 30 days waiting period, the WLC will be advised to read generally about hearing loss and its treatment.

The study protocol has been registered in the http://ClinicalTrials.gov Protocol Registration System and the registration number is NCT01611129 (Study ID Number FAS-IT-03).

### Outcome measures

The main outcome measure used will be the Hearing Handicap Questionnaire (HHQ) and the secondary outcome measures include the Hospital Anxiety and Depression Scale (HADS), the University of Rhode Island Change Assessment Scale (URICA) and the Hearing Disability Acceptance Questionnaire (HDAQ).

HHQ is an instrument which has 12 questions scored on a 5-point Likert scale (never, to almost always) and provides a measure of personal and social effects - emotional distress and discomfort, social withdrawal, and general restriction of participation. HHQ was developed on the basis of a questionnaire by Hétu *et al*. [27] and an unpublished general health scale - Glasgow Health Status Inventory [28]. HHQ has a good Cronbach’s alpha of 0.95 for the emotional and 0.93 for the social scale [29].

HADS is an instrument for screening for anxiety and depression [30]. The HADS consists of 14 items divided into two subscales (anxiety and depression). Each item is scored from 0 to 3 (0 = not at all, 3 = most of the time) with a total score of 0 to 21 per subscale. In general, HADS has good reliability and acceptable sensitivity and specificity [31].

URICA is a stages of change measure consisting of four sub-scales: pre-contemplation, contemplation, action and maintenance [32,33]. The original URICA scale consists of 32-items. However, in this study we use a modified version (‘the problem’ is replaced by ‘the hearing problem’) consisting of 24-item scale which has also been used in a number of studies [34,35]. This modified version focuses on pre-contemplation, contemplation, and action stages of change. Each item is rated on a 5-point Likert scale (1 = strong disagreement, 5 = strong agreement). Each sub-scale measures specific aspects. For example, the pre-contemplation scale is assumed to capture unwillingness to change a problem behaviour or ignorance regarding the problem; contemplation items assess whether the person is seriously considering change and/or considering the pros and cons of not changing; action items assess whether the individual is engaging in change; and maintenance items assess the degree that change is integrated into a person’s life. In addition, the subscales are combined arithmetically (contemplation + action + maintenance – pre-contemplation), which provides a secondary readiness to change score which can be used to assess readiness to change at entrance to treatment. The readiness score can range from −2.00 to +14.00, with higher scores representing greater motivation to change. A recent study by Laplante-Lévesque *et al*. which investigated the usage of the URICA scale in adults with acquired hearing impairments seeking help for the first time, showed good construct, concurrent and predictive validity of the scale [36].

HDAQ has been designed based on the Tinnitus Acceptance Questionnaire (TAQ) which was developed by Westin *et al*. [37] in Sweden. This is a measure of experiential avoidance/acceptance and consists of 12 items. Each of the 12 items is rated on a 7-point Likert scale (1 = never true, 7 = always true).

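### The URICA readiness score is defined with a maintenance term and a −2 to +14 range that do not match the three-stage, 24-item version the trial says it uses

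*Protocol article*

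**What the plan says.** All the scoring text stands in one paragraph of the protocol article, under Outcome measures.

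- URICA in general is described as "consisting of four sub-scales: pre-contemplation, contemplation, action and maintenance". On its length: "The original URICA scale consists of 32-items".
- The trial uses a modified form, "consisting of 24-item scale which has also been used in a number of studies". The next sentence reads: "This modified version focuses on pre-contemplation, contemplation, and action stages of change".
- Response format: "Each item is rated on a 5-point Likert scale (1 = strong disagreement, 5 = strong agreement".
- The paragraph then explains what each subscale captures, maintenance among them, and defines a secondary readiness score: "the subscales are combined arithmetically (contemplation + action + maintenance", with pre-contemplation subtracted.
- Range: "The readiness score can range from −2.00 to +14.00". Higher values mean more motivation to change. The score is described as usable on entry to treatment.

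The same section lists URICA as a secondary outcome; HHQ is the main one. Under Aim, hypothesis 3 states that the counseling tool "will result in increased readiness to change (or positively facilitate stages of change through hearing disability").

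**The concern.** The formula needs a maintenance subscale. The sentence describing the trial's own form names three stages, and maintenance is not one of them. The formula and its range therefore appear to belong to the four-subscale instrument described at the start of the paragraph.

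URICA is the only listed instrument that measures readiness to change, which is the subject of hypothesis 3. If the form lacks maintenance items, an analyst following the text has no value for one of the four terms. The analyst must then improvise by dropping the term, filling it in somehow, or turning to the separate subscales. With nothing fixed beforehand, that choice could be made after the data are seen. A three-term score could also be read against the wrong range or set beside published four-subscale values.

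**Working it through.** **Inputs, all from Outcome measures.** Items are scored 1 to 5. The original has 4 subscales and 32 items. The trial's form has 24 items and 3 named stages. The stated formula is C + A + M − PC (contemplation, action, maintenance, pre-contemplation), and the stated range is −2 to +14.

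**Step 1: reproduce the stated range.** A subscale mean of items scored 1 to 5 itself lies between 1 and 5, whatever the number of items.

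- Minimum of C + A + M − PC: 1 + 1 + 1 − 5 = −2
- Maximum: 5 + 5 + 5 − 1 = 14

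This matches exactly, so the stated range is correct arithmetic for four subscale means.

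**Step 2: rule out summed items.** Multiplying the bounds by the number of items per subscale gives:

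| Form | Minimum | Maximum |
|---|---|---|
| 4 subscales × 8 items | −16 | 112 |
| 4 subscales × 6 items | −12 | 84 |
| 3 subscales × 8 items | −24 | 72 |

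None gives −2 to +14. The score is built on subscale means, with maintenance included.

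**Step 3: the range for the three named subscales.**

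- Minimum of C + A − PC: 1 + 1 − 5 = −3
- Maximum: 5 + 5 − 1 = 9

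The width is 9 − (−3) = 12 points, against 14 − (−2) = 16 for the stated score. The midpoints differ as well: 3 + 3 − 3 = 3 on three subscales, and 3 + 3 + 3 − 3 = 6 on four. The two scores are on different scales.

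**Step 4: which form do the item counts suggest?** If items are divided equally (an assumption, since the article gives no split), 32/4 = 8 and 24/3 = 8. That fits the removal of one whole subscale. However, 24/4 = 6 is also a whole number, and a form with four subscales of 6 items would give −2 to +14 on means. The counts favor three subscales without settling the matter.

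**The case against.** The case for the protocol has four parts.

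- **Whether maintenance was dropped.** A reader might infer that the form certainly has no maintenance subscale and that the score can never be produced. The text does not go that far. It says where the modified version puts its focus, and it goes on to describe maintenance items. A form of 4 × 6 items would satisfy both the count and the range. This stands: the contradiction is certain, but which sentence is wrong is not.
- **Whether hypothesis 3 fails.** A reader might infer that hypothesis 3 cannot be tested. The composite is described for use at treatment entry and is never named as the endpoint for that hypothesis. The hypothesis also allows for movement through the stages of change, which the three subscales could address. This stands too.
- **Whether the treatment comparison is biased.** A reader might take the missing maintenance mean, 1 to 5 points per person, as a scoring error that distorts the result. It is not one. Both arms would be scored by the same rule, and the analysis of covariance under Data collection and analysis does not use the theoretical range. The gap matters only for reading scores against the stated range or against four-subscale values.
- **Whether this belongs in an analysis plan.** Scoring detail may properly be left to such a plan. Here, though, the article states a formula and a range that conflict with its own account of the instrument, so this is not an omission. This part does not stand.

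**Conclusion.** The point holds as an internal contradiction in the definition of a secondary outcome. The readiness formula and its −2 to +14 range require four subscale means, while the form described names three stages. If only those three are administered, which is the natural reading, the score cannot be computed as written. The computable version then runs from −3 to +9: the stated maximum is 5 points too high (14 − 9) and the stated minimum 1 point too high (−2 against −3). If maintenance items are in the form, the formula and range are right and the three-stage sentence is wrong. Either way, one statement needs correcting.

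The three-subscale figures assume scoring by subscale means, which the exact match in the working supports, and a form without maintenance, which the text suggests but does not prove. Severity is moderate. The primary HHQ analysis and the sample size, which is calculated from HHQ alone, do not depend on URICA, and a between-group comparison scored consistently in both arms would not be biased by this.

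**What to change.** First confirm which subscales are administered. Trial status says that recruitment is complete and the trial is running, so this can be checked against the online questionnaire itself. Then:

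- **If three subscales:** define readiness as contemplation + action − pre-contemplation on subscale means, range −3 to +9. Delete the maintenance term and the −2 to +14 range, and note that the score is not comparable with four-subscale values.
- **If maintenance items are included:** keep the formula and range, and correct the sentence that limits the modified version to three stages.

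In both cases, state before analysis whether hypothesis 3 is tested on the composite or on the subscales.

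The cost is a few sentences and, at most, a change to the scoring code. No data collection changes. In the three-subscale case comparability with the 32-item composite is lost, but the choice of the shorter form already implies that. Maintenance should not be deleted before the check, because doing so would discard collected data if those items are in use.
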